### Secondary endpoints

To evaluate the effect of IMT on respiratory muscle function and lung function, participants will undergo measurements at five time points (baseline (T0), the day before surgery (T1), and during hospital stay on postoperative day 3 (T2), day 6 (T3), and day 9 (T4) (Figure 1)). Forced expiratory volume in 1 second (FEV_1_) and forced vital capacity (FVC) are assessed using a portable spirometer. Respiratory muscle function will be evaluated using maximal inspiratory pressure (Pi_max_) and inspiratory muscle endurance (Pi_end_). Pi_max_ is measured at the mouth with a forceful inspiratory maneuver at residual volume. To measure Pi_end_ patients will be asked to breathe against an inspiratory load of 70% Pi_max_ until task failure (with a minimum of 3 minutes and a maximum of 7 minutes at baseline). All measurements are performed in the seated position.

To determine an effect of IMT on quality of life (QoL) the EuroQol-5D and the SF-12 are assessed at baseline and 4 weeks after surgery. Postoperative pulmonary complications other than pneumonia are scored postoperatively (for example, positive sputum cultures) as well as other postoperative complications (anastomotic leakage, chylus leakage, wound infection, cardiac complications, sepsis, vocal cord paralysis, critical illness polyneuropathy).

Other secondary endpoints are in-hospital mortality, length of postoperative hospital stay (starting on the day of surgery), mechanical ventilation time (number of hours spent on the mechanical ventilator during and directly following the primary surgery), and number of re-intubations.

**Figure 1 F1:**
[figure not shown]
Flowchart of PREPARE procedures.

### Other outcome measures

The following variables will be obtained from the patients’ medical records: discharge location (home, rehabilitation center, nursing home, other hospital, hospice), operation details (duration, location, technique, anastomosis, single/double lung ventilation, use of mini-tracheal cannula, blood loss, re-operation), mechanical ventilation details (duration, re-intubation), tumor type, Mandard score (tumor regression grade), classification of malignant tumors (TNM score), and date of first postoperative mobilization (active, standing aid, passive lift).

### Education and monitoring

All involved healthcare providers are well informed about the study procedures. Surgeons and specialized nurses providing the initial information about the PREPARE trial are personally informed about the aims and procedures of the study and their tasks within the trial by the coordinating researcher. The research group organized an afternoon meeting where the local assessors and PTs attended practical workshops about the procedures and use of all equipment. Additional written information is provided as well. Study procedures will be monitored by an independent monitor in the coordinating center and by the coordinating researcher in the participating centers during multiple monitoring visits (at the start of the trial, after the first three completed patients, after 1 year, and at the end of the trial).

### Sample size calculation

Sample size is calculated based on an expected reduction of 50% on the incidence of postoperative pneumonia [13]. Assuming a 30% incidence of postoperative pneumonia after esophageal resection in the control arm and using a significance level of 0.05 and a power of 80%, 118 patients are required in each arm [2,15,23]. Taking into account a 5% in-hospital mortality rate after surgery, approximately 124 patients per arm need to be included (248 patients in total).

### Statistical analyses

Data analyses will be performed in accordance with the intention to treat principle. IBM SPSS statistics software (version 20 or higher) will be used for data analyses. A two-sided *P* value of less than 0.05 is regarded to be statistically significant. Analyses will be adjusted for center.

Literature shows that the odds ratio (OR) can be interpreted as relative risk (RR) when the incidence of the outcome is < 10%. When the incidence is high, the OR can overestimate the RR [24-26]. Therefore, analyses of dichotomous variables will be performed using logistic regression analysis when the incidence is ≤ 10% and with Log-binomial regression analysis in the case of an incidence of > 10%. The incidence of pneumonia will be compared between the two groups and results will be presented as OR or RR with a 95% confidence interval (CI). The risk difference and numbers needed to treat will also be calculated when significant differences are found between groups.

For the continuous secondary outcome measures duration of mechanical ventilation and length of stay (ICU and total), survival analysis (Cox proportional hazards regression model) will be used to determine differences in time to extubation and discharge. For the categorical secondary outcome measures other pulmonary complications and in-hospital mortality the OR or RR will be calculated. Other outcomes (for example, lung function, respiratory muscle function, quality of life) will be compared between groups using linear regression for parametric data or the Mann–Whitney U Test for non-parametric data. To determine differences between time points in lung function and respiratory muscle function, results will be analyzed using the repeated measurements method (General Linear Modeling Repeated Measures). In case of missing measurements or covariates, multiple imputations will be performed.

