### Study design and setting

This study is conducted as a single-blind multicenter RCT and will be coordinated by the University Medical Center Utrecht (UMCU) (Department of Rehabilitation, Nursing Science & Sports and Department of Surgery). Patients are randomly assigned to either care as usual without IMT or to IMT as an addition to care as usual. The randomization procedure is performed by a flexible web-based randomization system. The assignment sequence will be concealed. Randomization is stratified by center and minimization techniques are applied for surgical technique (transhiatal esophageal resection, transthoracic esophageal resection, minimally invasive esophageal resection).

This study is funded by ‘NutsOhra Foundation’ and ‘The Friends of the UMC Utrecht Foundation’ , and will be conducted in accordance with the principles of the Declaration of Helsinki and Good Clinical Practice Guidelines. The independent ethics committee of the UMCU has approved the study. Written informed consent will be obtained from all participating patients.

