## Discussion

The high incidence of pneumonia has large impact on postoperative outcomes after esophageal resection. Mortality rates are significantly higher compared to patients without pneumonia (20% *versus* 3%) [6] and the use of healthcare is substantially increased by extended duration of hospital stay associated with increased healthcare costs [5,7,8]. Furthermore, postoperative complications have a negative influence on long-term quality of life [27,28]. Less invasive surgical techniques attribute significantly to decreasing this high impact complication which is of high clinical relevance [4]. Preoperative IMT resulted in a reduction of 50% of postoperative pneumonia in cardiac surgery patients and might be a promising intervention to further reduce the incidence of postoperative pneumonia after esophageal resection [13]. The PREPARE study is the first multicenter RCT investigating the effect of this intervention in esophageal resection candidates.

Methodological decisions of the PREPARE trial are compared with strengths and weaknesses of other studies (since 2000) investigating the effect of preoperative IMT (Table 2).

**Table 2 T2:** Overview of preoperative inspiratory muscle training studies

	**PREPARE trial**	**Dettling **[15]	**Agrelli **[29]	**Hulzebos **[13]	**Savci **[30]	**Dronkers **[16]	**Barbalho-Moulim **[31]	**Kulkarni **[32]
**Study population**	Esophageal resection	Esophageal resection	Esophageal resection	Cardiac surgery	Cardiac surgery	Upper abdominal surgery	Open bariatric surgery	Major abdominal surgery
**Number of (anticipated) included patients**	(248)	83	20	279	43	20	22	80
**Sample size calculation**	+	-	-	-	-	-	-	-
**Randomization**	Individual	-	-	Individual	Individual	Individual	Individual	Individual
**Control group without IMT**	+	+	-	+	+	+	+	+
**Pilot-study**	-	+	+	-	-	+	-	+
**Blinding**	Primary and secondary outcomes	-	-	Primary outcome	-	Primary outcome	-	-
**Multicenter**	+	-	-	-	-	-	-	-
**Stratification**	Center and surgical technique	-	-	-	-	-	-	-
**Pulmonary risk stratification**	-	-	-	+	-	+	-	-

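### Allocation is balanced on centre and surgical technique, but the stated adjustment covers centre alone, which can make the primary test mildly conservative

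*Protocol article*

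**What the plan says.** Study design and setting: "Randomization is stratified by center and minimization techniques are applied for surgical technique". Technique has three levels: transhiatal, transthoracic and minimally invasive. The Stratification row of Table 2 in the Discussion gives the same two factors for this trial: "Center and surgical technique".

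Statistical analyses: "Analyses will be adjusted for center". No other adjustment covariate is named for the primary or any secondary analysis, and no reason is given for leaving technique out. The same section plans logistic regression for binary outcomes with incidence up to 10% and log-binomial regression above that. It plans Cox models for ventilation time and length of stay, and linear regression or the Mann-Whitney U test for the other outcomes. Tests are two-sided at 0.05.

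On whether technique is prognostic, the Discussion says of pneumonia: "Less invasive surgical techniques attribute significantly to decreasing this high impact complication which is of high clinical relevance".

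**The concern.** Balancing the arms on a prognostic factor makes the treatment estimate less variable than it would be under simple randomisation. A model that includes the factor reflects that gain. A model that omits it leaves the factor's variation in the residual, so the reported standard error is larger than the true one. P values are then too large on average and intervals too wide.

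The trial is sized at 80% power with little reserve, so precision gained in the allocation and given up in the analysis is worth recovering. The adjustment set should also be settled in advance. Odds ratios and hazard ratios change with the covariates in the model even under perfect balance, so adding technique after unblinding would look selective.

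**Working it through.** **The plan's own figure.** Sample size calculation: "using a significance level of 0.05 and a power of 80%, 118 patients are required in each arm". For 30% against 15%, the unpooled formula gives (1.960 + 0.842)² × (0.30 × 0.70 + 0.15 × 0.85) / 0.15² = 117.7, so 118 per arm, as stated. Adding 5% gives 118 × 1.05 = 123.9, so 124 per arm and 248 in total, also as stated. (Dividing by 0.95 gives 124.2, so 125; the difference is immaterial.) The formula contains no covariates, so this point does not change the required number.

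**Assumptions.** The article gives neither pneumonia rates by technique nor the technique mix. Both are assumed below, in the order transhiatal / transthoracic / minimally invasive. Technique shares are 20/30/50% and N = 248 over eight centres.
- Moderate effect: control rates 25/42/25%. Average 0.2 × 0.25 + 0.3 × 0.42 + 0.5 × 0.25 = 0.301.
- Strong effect: control rates 20/60/16%. Average 0.2 × 0.20 + 0.3 × 0.60 + 0.5 × 0.16 = 0.300.

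Both averages agree with the protocol's 30%.

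**Approximate size by hand, technique varying within centres.** Let V be the total variance, p(1 − p), and B the part lying between techniques. With near-perfect balance, the true standard error is √((V − B)/V) times the one reported when technique is omitted.
- Moderate: B = 0.2 × 0.051² + 0.3 × 0.119² + 0.5 × 0.051² = 0.0061 and V = 0.301 × 0.699 = 0.2104. The ratio is √0.971 = 0.985. The effective critical value is 1.96 / 0.985 = 1.99, so the size is about 4.7%.
- Strong: B = 0.2 × 0.10² + 0.3 × 0.30² + 0.5 × 0.14² = 0.0388 and V = 0.2100. The ratio is √0.815 = 0.903. The effective critical value is 1.96 / 0.903 = 2.17, so the size is about 3.0%.

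**Simulation.** 2,000 trials per cell, biased-coin minimisation on technique within centre (probability 0.8), and a risk-ratio model fitted as Poisson regression with robust variance. Power is for a risk ratio of 0.5. Simulation error is about 0.005 on size and 0.009 on power.

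| Technique effect | Technique and centre | Size, centre | Size, centre + technique | Power, centre | Power, centre + technique |
|---|---|---|---|---|---|
| None (30% throughout) | mixed | 0.054 | 0.054 | 0.818 | 0.822 |
| Moderate | mixed | 0.047 | 0.052 | 0.803 | 0.812 |
| Strong | mixed | 0.029 | 0.050 | 0.843 | 0.871 |
| Moderate | mostly by centre | 0.052 | 0.052 | 0.842 | 0.839 |
| Strong | mostly by centre | 0.052 | 0.050 | 0.891 | 0.895 |

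The mixed rows agree with the hand calculation (0.047 and 0.030). Power should be compared only within a row, because the average control rate differs between rows. Logistic models gave the same pattern.

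**Other assumed inputs.** A separate simulation (1,500 trials per scenario, shares 25/35/40%) gave centre-only size 4.5% and power 80.7% against 81.8% with technique, for rates 25/45/20%. For rates 30/55/12% it gave 3.6%, and 84.3% against 86.6%. The model with technique rejected 5.8% under the null in both scenarios. With a simulation error of about 0.6 points, that is compatible with 5%, but part of the power gain in those runs may reflect the higher realised size. A further set of 2,000 runs per cell gave size 4.6% and power 82% against 83% (moderate), and 3.5% and 84% against 87% (strong). It showed no meaningful difference when technique mostly followed centre.

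**The case against.** **The effect may be nil here.** The Discussion says that each centre has its own surgical protocol. If technique mostly follows centre, adjusting for centre already captures it, and the last two rows of the table show no material loss. The larger figures need a strong technique effect and free variation within centres, neither of which the article documents. This stands, and it limits the size of the point.

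**The article may not mean centre alone.** It does not use the word only, it provides for imputing missing covariates, and a condensed article can leave a fuller list to the analysis plan. This is fair but not decisive: the article does state an adjustment set, and that set names one balancing factor and omits the other.

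**Adding technique is not free.** The simulations above used robust Poisson regression, which avoids the convergence failures of the planned log-binomial model. In a simulation of the log-binomial model itself (1,500 runs per cell, unequal centre sizes assumed), usable fits fell when technique was added. With technique mixed within centres they went from 94% to 91% (rates 25/45/20%) and from 95% to 90% (30/55/12%). With technique mostly by centre they went from 87% to 79% and from 73% to 65%. The levels depend on the assumed centre sizes and convergence criterion, but the direction was the same in every cell. This stands, so a fallback is needed.

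**It cannot apply everywhere.** The Mann-Whitney test takes no covariates. At the 5% mortality in the Sample size calculation, 248 × 0.05 = 12.4, so about 12 deaths would have to support one treatment, seven centre and two technique terms. This also stands.

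**Conclusion.** The mismatch between allocation and analysis is real and worth correcting, but its consequence is modest. With technique prognostic and varying within centres, the centre-only test has a size of roughly 3% to 4.7% and gives up about 1 to 3 points of power. With technique largely determined by centre, nothing material is lost. All of this rests on assumed technique rates and mix; the only documentary support for a technique effect is the Discussion's statement, which carries no figure.

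Three stronger readings are not supported:
- A reader might infer that the 5% test is invalid. The departure is towards conservatism, is within simulation error for a moderate effect, and does not inflate false positives. Balance is kept, so the omission does not favour either arm.
- A reader might infer that technique was chosen for minimisation because it predicts pneumonia. The article gives no reason for the choice. The argument needs only that technique is prognostic.
- A reader might infer that every between-group comparison must carry both factors at no cost. The Mann-Whitney test cannot, sparse outcomes should not, and the log-binomial model becomes somewhat harder to fit.

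**What to change.** In Statistical analyses, replace the adjustment sentence with wording such as: *The primary pneumonia model and the secondary regression models (Cox, linear, and binary models with enough events) are adjusted for centre and for the planned surgical technique recorded at randomisation (transhiatal, transthoracic, minimally invasive). If the log-binomial model does not converge, Poisson regression with robust variance and the same covariates is used. Mann-Whitney tests and very sparse outcomes such as in-hospital mortality are not adjusted for these factors.*

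Use planned technique and not the technique performed, which is determined after randomisation. Randomisation follows the baseline visit and precedes surgery, so the planned technique is what the minimisation must use and should already be held in the randomisation system.

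The cost is a few sentences, two more model terms and a slightly higher chance of needing the fallback. The sample size and data collection do not change.

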### Baseline assessment and follow-up measurements

The patient characteristics age, weight, height, gender, daily work, highest education, civil status, and preoperative physical therapy guidance (outside trial context) are prospectively recorded by means of a standardized interview during the baseline assessment. Data obtained from the patients’ medical records include history of COPD, smoking, pneumonia, diabetes mellitus, productive cough and cardiac events, tumor location, neoadjuvant treatment, prophylactic antibiotics, American Society of Anesthesiologists (ASA) score, admission and discharges dates, operation technique.

To evaluate the effect of IMT on respiratory muscle function and lung function, participants undergo measurements at five time points (baseline (T0), the day before surgery (T1), and during hospital stay on postoperative day 3 (T2), day 6 (T3), and day 9 (T4)). To determine an effect of IMT on quality of life (QoL) the EuroQol-5D and the SF-12 are assessed at baseline and 4 weeks after surgery. See for detailed description the paragraph secondary endpoints.

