The PREPARE study is the only study reporting a priori sample size calculation, and is unique in esophageal resection candidates with sufficient statistical power to show reductions in pneumonia events. All esophageal resection candidates are included in the PREPARE trial without considering individual risk for PPCs since at this point little is known about which patients will benefit the most from preoperative IMT. This is in contrast with two earlier studies who selected candidates for preoperative IMT based on a risk score for PPCs [13,16].

IMT is a simple intervention that is well tolerated by patients [33]. The researchers have chosen a home-based IMT program with guidance from a distance using weekly telephone consultations. This deviation of the other protocols where one training session a week is supervised (see Table 2) was chosen to decrease the burden for the patients and to increase inclusion rates. Patients often have to travel 30 minutes or more to reach the hospital. The standpoint of the PREPARE trial is that the intervention should fit in with daily care practice and with daily life of the patient. A weekly in-hospital physical therapy session of no more than 30 minutes (one high intensity training sessions of 30 breaths will take no more than 5 minutes) will discourage patients to participate in the trial or in an IMT program in general. Based on years of experience in guiding patients in performing their home-based IMT program, the PREPARE team presumes that clear instructions at baseline, an instruction video and the weekly telephone consultations should be sufficient to guide the patients and to monitor patient compliance. Furthermore, the memory of the digital inspiratory muscle trainer (POWERbreathe K3-series) enables the PTs to compare the last 36 trainings sessions with the recorded data in the patient diary which enables a supplementary check on patient compliance and adequate adjustment of the training load.

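### The primary pneumonia analysis names center as its only covariate; adding surgical technique and two or three recorded baseline variables could gain up to about 6 power points, or nothing, at little cost

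*Protocol article*

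**What the plan says.** In the Protocol article, Statistical analyses, adjustment is covered by one sentence: "Analyses will be adjusted for center". It precedes the model descriptions, so it applies to the pneumonia comparison (log-binomial when incidence exceeds 10%) and to the Cox models for ventilation time and length of stay. The same section provides multiple imputation for missing covariates but does not say which covariates are meant.

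On allocation, Study design and setting says: "Randomization is stratified by center and minimization techniques are applied for surgical technique". Pulmonary risk plays no part, and Table 2 in the Discussion gives PREPARE a minus in the row "Pulmonary risk stratification".

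On data collection, Baseline assessment and follow-up measurements says: "Data obtained from the patients’ medical records include history of COPD, smoking, pneumonia, diabetes mellitus, productive cough and cardiac events". It also lists age and ASA score. Secondary endpoints adds FEV1, FVC and maximal inspiratory pressure at T0. Recruitment and informed consent places the baseline measurement before randomization.

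On the population, the Discussion says: "All esophageal resection candidates are included in the PREPARE trial without considering individual risk for PPCs". It contrasts this with two earlier studies that "selected candidates for preoperative IMT based on a risk score for PPCs".

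**The concern.** The trial admits patients across the whole range of pulmonary risk and records several plausible predictors of pneumonia. It uses none of them in the allocation or in the stated primary model. The article itself gives some weight to pulmonary risk: it describes the cardiac surgery result in high-risk patients and notes that earlier trials selected on a risk score. If these variables do predict pneumonia here, a prespecified adjustment would narrow the interval of the risk ratio and limit the influence of a chance imbalance in, say, COPD.

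Surgical technique is a related gap. It is a minimization factor, and the Discussion links less invasive techniques to fewer pneumonias, but the adjustment sentence leaves it out. Ignoring an allocation factor that is prognostic tends to make the standard error too large.

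The trial is sized at 80% power for a halving of pneumonia, so there is little reserve. Covariates chosen only after an imbalance has been seen would be open to challenge.

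**Working it through.** **1. The plan's own figure.** Inputs from Sample size calculation and Statistical analyses: 30% in the control arm, a 50% reduction (so 15%), two-sided 0.05, power 80%. With unpooled variances:

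n = (1.960 + 0.842)² × (0.30×0.70 + 0.15×0.85) / 0.15² = 7.849 × 0.3375 / 0.0225 = 117.7, i.e. 118 per arm.

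This matches the article. The pooled form gives 121. At 124 per arm the pooled formula gives 81.1% power with no covariates. The trial therefore meets its target on its own inputs.

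**2. Gain for the risk ratio.** The documents give no prognostic strength, so it is varied. Setup: 118 per arm, 8 equal centers, 30% v 15%, marginal risk ratio by standardization from a logistic model. The analysis with center only is compared with center plus three covariates, one carrying signal and two pure noise. There were 4,000 trials per setting in the first two rows and 3,000 in the others.

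| Assumed AUC | Power, center only | Power, adjusted | SE of log RR, center only → adjusted | (SE ratio)² |
|---|---|---|---|---|
| 0.56 | 78.7% | 78.8% | 0.271 → 0.272 | 0.99 |
| 0.61 | 79.5% | 80.5% | 0.267 → 0.267 | 1.00 |
| 0.66 | 78–79% | 81.0% | 0.271 → 0.267 | 1.03 |
| 0.70 | 78–79% | 83.6% | 0.269 → 0.259 | 1.08 |
| 0.74 | 78–79% | 84.6% | 0.268 → 0.253 | 1.12 |

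The last column is the equivalent sample-size factor. For example, (0.268/0.253)² = 1.12, or about 30 of 248 patients; 1.08 is about 20 and 1.03 about 7. Type I error at 30% v 30% was 4.7% to 4.9% in the last three settings. Monte Carlo error is about √(0.8×0.2/3000) = 0.7 points for a single power figure.

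**3. Cross-check with a different model.** Modified Poisson at 124 per arm with one covariate:

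- OR 1.6 per SD: SE 0.259 → 0.255, power 80.4% → 81.9%, (0.259/0.255)² = 1.03.
- OR 2.0 per SD: SE 0.260 → 0.252, power 81.1% → 84.2%, factor 1.06.
- OR 2.5 per SD: SE 0.260 → 0.247, power 80.5% → 85.8%, factor 1.11.

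The two approaches agree on size.

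**4. Can the named model carry the covariates?** Log-binomial fits with treatment and 8 centers failed or were invalid in 0% of simulated trials with no extra covariate, 17% with one continuous covariate and 45% with three. This assumed 0.5 log-odds per SD for each covariate and was fitted in Python. SPSS, which the article names, may differ in detail.

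**5. Room in the data.** Expected events are 22.5% × 236 = 53 (or × 248 = 56). Treatment (1), centers (7), technique (2) and three single-term baseline variables (3) make 13 coefficients, about 4 events each. That is a reason to keep the list short. The simulations in step 2 had 11 coefficients and did not include technique.

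**6. Cox models.** With an assumed conditional hazard ratio of 1.43 (log 0.358) and a covariate hazard ratio of 1.5 per SD, the SE goes from 0.1327 to 0.1338. The estimate moves from 0.315 to 0.359 and power rises from 67% to 79%. At 1.25 per SD, power rises from 75% to 77%. The SE does not fall. The target becomes a conditional hazard ratio, and the benefit is power.

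**The case against.** The strongest reply is that nothing here is wrong. A center-adjusted comparison is valid, holds its type I error and reaches about the power the trial was designed for. On this view the request is for more efficiency than the design needs. The validity part stands in full.

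Second, the article does not say that center is the only covariate. It mentions imputing missing covariates, and a list may exist in an analysis plan that is not shown. That stands as a limit on wording: center is the only variable named. The point survives because the article states an adjustment set and does not leave it open.

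Third, prognostic strength in esophageal resection is not established by the article. The risk-score trials were in cardiac and upper abdominal surgery, and the Discussion's remark on how little is known concerns who benefits, which is effect modification. This stands, and it is why the range of gain has to start at zero.

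Fourth, the change is more than one added term. It replaces the log-binomial fit, it should include surgical technique, and smoking is listed without saying whether current smoking is recorded. All of this is accepted in the fix.

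**Conclusion.** The point holds as a modest improvement in efficiency. For the risk ratio the gain runs from nil at AUC about 0.56 to 0.61 to about 2 to 6 power points at AUC 0.66 to 0.74, equal to about 3% to 12% more patients. The whole range rests on assumed prognostic strength and on the planning rates of 30% and 15%.

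A reader might infer more, and the documents do not support it:

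- That the primary estimate is biased, or that randomization leaves pulmonary risk unbalanced. These factors are not stratified or minimized, but randomization balances them in expectation, and chance imbalance is already reflected in the confidence interval.
- That the trial is underpowered. Its sample size reproduces.
- That precision is certainly being lost. With weak predictors nothing is lost.
- That adjustment would sharpen the Cox estimates. Their standard errors do not fall.

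**What to change.** Amend Statistical analyses so that the primary pneumonia analysis adjusts for center, surgical technique and two or three baseline variables fixed before unblinding. Candidates are age, baseline FEV1 or history of COPD, and smoking as it is actually recorded. Estimate the marginal risk ratio and risk difference by standardization from a logistic model, or use modified Poisson for the risk ratio, in place of log-binomial. Keep the center-only analysis as a sensitivity analysis.

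If the same covariates enter the Cox models, state that the hazard ratio is then conditional and that the benefit is power, not a smaller standard error.

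The cost is small. No new measurements are needed, and Trial status shows recruitment still open. The downsides are a change from the named model, a list that must be fixed in advance, and imputation of a few missing baseline values. With about 53 expected events, two baseline variables are safer than three. A short simulation of the final model with the technique terms included would confirm that type I error is held.

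### The risk difference and NNT are planned only for a significant result, so a null trial would have no planned absolute effect estimate

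*Protocol article*

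**What the plan says.** Three statements in the Statistical analyses section bear on this.

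- The pneumonia comparison is always reported on a relative scale: "results will be presented as OR or RR with a 95% confidence interval (CI"). No condition is attached.
- The absolute scale is conditional: "The risk difference and numbers needed to treat will also be calculated when significant differences are found between groups".
- The condition is the two-sided P value: a "value of less than 0.05 is regarded to be statistically significant".

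The same section says that analyses are adjusted for center. No other section of the article provides an absolute effect measure for a non-significant result.

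The Sample size calculation section gives the design assumptions: "Assuming a 30% incidence of postoperative pneumonia after esophageal resection in the control arm", an "expected reduction of 50% on the incidence of postoperative pneumonia", and the resulting number, "118 patients are required in each arm".

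**The concern.** Whether an estimate is calculated should not depend on what it shows. Under this rule the risk difference and NNT exist only for results that pass P < 0.05, in either direction. Two things follow.

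1. A non-significant trial has no planned absolute estimate or interval. That is when a clinical reader most wants to know which absolute benefits remain compatible with the data.
2. Across repeated trials run under the rule, the absolute effects that get reported are a selected subset and on average larger than the truth.

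The rule is written out in the current text, so this is not a detail left to an analysis plan or lost when the article was condensed.

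Effects smaller than the planned halving are plausible on the article's own account. The Background says that the reduction of over 50% was seen in cardiac patients at high pulmonary risk, and that a non-randomized pilot study in esophageal resection showed no effect on pulmonary outcome. The Discussion says that PREPARE takes all candidates regardless of risk.

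**Working it through.** **Inputs.** From the Sample size calculation section: control incidence 30%, relative reduction 50% (so 15% with IMT), alpha 0.05, power 80%, 118 per arm before inflation and about 124 after. From the Statistical analyses section: the two-sided 0.05 threshold. IMT incidences other than 15% are assumptions used to show a range.

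**Step 1. The plan's own figure.** With two proportions, a two-sided test and unpooled variance:

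n = (1.960 + 0.842)² × (0.30×0.70 + 0.15×0.85) / 0.15² = 7.849 × 0.3375 / 0.0225 = 117.7, rounded up to 118.

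This reproduces the stated 118. The implied design difference is 30 − 15 = 15 points, NNT 1/0.15 = 6.7.

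**Step 2. What the condition does.** All outcomes of two binomials with 118 per arm were enumerated. The condition was a pooled two-sided z-test at 0.05, not adjusted for center. The table gives the chance of a significant result and the mean risk difference among results significant in favor of IMT.

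| True IMT rate | True difference (NNT) | P(significant) | No absolute estimate | Mean reported difference (NNT) | Ratio |
|---|---|---|---|---|---|
| 15% (design) | 15.0 points (6.7) | 0.80 | 20% | 16.9 points (5.9) | 1.13 |
| 20% (assumed) | 10.0 points (10) | 0.43 | 57% | 15.1 points (6.6) | 1.51 |
| 22.5% (assumed, RR 0.75) | 7.5 points (13.3) | 0.26 | 74% | 14.6 points (6.8) | 1.95 |
| 25% (assumed) | 5.0 points (20) | 0.14 | 86% | 14.3 points (7.0) | 2.86 |

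Check on the design row: the mean difference in the non-significant trials is 7.6 points, and 0.798×16.88 + 0.202×7.58 = 15.0. So the estimator is unbiased over all trials, and the gap comes from which trials report it.

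With 124 per arm the design row changes little: 82% significant, mean 16.7 points, ratio 1.11.

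**Step 3. Smallest absolute benefit that could be reported.** Take 35/118 control events. With 22 IMT events the difference is 13/118 = 11.0 points and z = 0.1102 / √(0.2415×0.7585×2/118) = 1.98, which passes. With 23 events the difference is 10.2 points and z = 1.81, which does not. At that control rate no absolute benefit below 11 points would be calculated.

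**Step 4. A null result under the rule.** Observed 30% v 22%, 118 per arm:

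- Risk difference: 0.08 ± 1.96 × √(0.30×0.70/118 + 0.22×0.78/118) = 0.08 ± 0.111, that is -3 to 19 points. It includes both zero and the 15-point design difference. The plan would not calculate it.
- RR, using 35/118 and 26/118: 26/35 = 0.74. SE of log RR = √(1/26 − 1/118 + 1/35 − 1/118) = 0.224, so the 95% CI is 0.48 to 1.15. The plan would report this.

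**The case against.** The strongest reply is that nothing essential is hidden. The OR or RR with its 95% CI is reported on every outcome, and in the example above the interval 0.48 to 1.15 contains both 1 and the design RR of 0.50. A reader might infer from the rule that a null PREPARE trial could not be told apart from an imprecise one. The documents do not support that, because the relative interval already shows the imprecision. This part of the reply stands.

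A reader might also infer that the rule makes this trial's own risk difference or NNT too favorable. It does not. In any one significant trial the value is the same with or without the condition, and the RR in those trials is subject to the same selection by significance. The inflation in Step 2 is a long-run average. It is about 1.13 at the design effect and nears twofold only if the true effect is about half of what was planned. This stands too.

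Nor was the sample size stated in absolute terms. The target is a relative one ("Sample size is calculated based on an expected reduction of 50% on the incidence of postoperative pneumonia"), from which the 15 points follow given a 30% control rate. The RR addresses that target directly.

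Finally, withholding an NNT from a null result is defensible. For -3 to 19 points the NNT interval would run from about 5 (1/0.191) through infinity to a number needed to harm of about 32 (1/0.031).

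What does not stand is the extension of that argument to the risk difference, which behaves well around zero. A relative interval is not an absolute one, and a reader given the arm counts could derive only a crude difference, whereas the plan adjusts its analyses for center.

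**Conclusion.** The point holds as a reporting flaw, minor to moderate in weight. The plan makes an effect estimate depend on the P value, so the absolute effect is available only for significant results. At the design effect this leaves about 20% of trials without a planned absolute estimate, and the values reported average 16.9 points against a true 15. Both figures worsen if the true effect is smaller. A null result would lack its planned absolute interval.

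The primary test, type I error, sample size and relative estimate are untouched. The percentages rest on a 30% control rate, 118 evaluable per arm and an unadjusted test. Adjustment for center, or a control rate other than 30%, would shift them somewhat. The existence of the condition depends on none of these assumptions.

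**What to change.** Replace the conditional sentence with:

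> The risk difference with 95% CI, adjusted for center as for the other analyses, will be reported for pneumonia and the other dichotomous outcomes whatever the P value; the NNT will be given only when the risk-difference CI excludes zero.

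Keeping a condition on the NNT is acceptable because the NNT is only the reciprocal of a risk difference that is now always shown with its interval.

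The cost is one sentence and a few lines of output. It needs no new data, no further patients and no change to the primary test. The logistic and log-binomial models do not return a risk difference directly, so the method for the center-adjusted difference should be named at the same time, for example a Mantel–Haenszel risk difference stratified by center, or standardization from the fitted model. The change should be made before results are known, since adding the absolute effect afterwards would itself be a choice made in view of the result.
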